## Abstract

**Background:**

Older adults, who are living in nursing homes that provide a high level of long-term nursing care, are characterized by multimorbidity and a high prevalence of dependency in activities of daily living. Results of recent studies indicate positive effects of structured exercise programs during long-term care for physical functioning, cognition, and psychosocial well-being. However, for frail elderly the evidence remains inconsistent. There are no evidence-based guidelines for exercises for nursing home residents that consider their individual deficits and capacities. Therefore, high-quality studies are required to examine the efficacy of exercise interventions for this multimorbid target group. The purpose of this study is to determine the feasibility and efficacy of a multicomponent exercise intervention for nursing home residents that aims to improve physical and cognitive functioning as well as quality of life.

**Methods:**

A two-arm single-blinded multicenter randomized controlled trial will be conducted, including 48 nursing homes in eight regions of Germany with an estimated sample size of 1120 individuals. Participants will be randomly assigned to either a training or a waiting time control group. For a period of 16 weeks the training group will meet twice a week for group-based sessions (45–60 min each), which will contain exercises to improve physical functioning (strength, endurance, balance, flexibility) and cognitive-motor skills (dual-task). The intervention is organized as a progressive challenge which is successively adapted to the residents’ capacities. Physical functioning, cognitive performance, and quality of life will be assessed in both study groups at baseline (pre-test), after 16-weeks (post-treatment), and after 32-weeks (retention test, intervention group only).

**Discussion:**

This study will provide information about the efficacy of a multicomponent exercise program in nursing homes (performance, recruitment). Results from this trial will contribute to the evidence of multicomponent exercises, which specifically focus on cognitive-motor approaches in the maintenance of mental and physical functioning. In addition, it will help to encourage older adults to actively engage in social life. Furthermore, the findings will lead to recommendations for health promotion interventions for frail nursing home residents.

**Trial registration:**

The trial was prospectively registered at DRKS.de with the registration number DRKS00014957 on October 9, 2018.

## Background

The worldwide population is progressively aging, which is why an increased demand for long-term care is expected [1]. Aging is associated with a decline in physical and cognitive functioning as well as with an increased occurrence of adverse health events. Consequently, the prevalence of disabilities increases substantially in the aging population, particularly after the age of 85 [2]. The condition of old people living in nursing homes is often characterized as multimorbidity at high risk of disability onset or progression [3]. This might lead to a loss of independence in activities of daily living (ADL), which is often closely associated with institutionalization and death [4]. Moreover, the declining physical functional status affects the overall quality of life of older adults [3]. Thus, effective interventions to strengthen health resources and prevent or delay disabilities and the loss of physical and cognitive functioning in older institutionalized people is a public health priority [3].

With the German Prevention Act of 2015, German nursing care insurances must provide preventive services in nursing homes that are aiming at promoting the health of residents by maintaining or improving several domains, such as physical functioning and mobility, cognition and quality of life [5]. The PROCARE project uses the BASE-program [6] to provide a strategy for the health promotion process described in the prevention guidelines [5].

The current project focusses on improving the above-mentioned goals. Therefore, a multicomponent exercise intervention program that takes the desires and preferences of the residents into account will be conducted. There is strong evidence that structured exercise programs in healthy and pre-frail older individuals can effectively improve everyday functionality, mobility, while reducing falls and physical frailty [7–12]. In addition, the positive effect of regular physical activity on cognition and on the prevention of diseases (such as cardiovascular diseases, diabetes, osteoporosis or sarcopenia) has already been demonstrated [1, 13–16]. In contrast, evidence from exercise interventions in the nursing home setting is less clear and inconsistent. A systematic review [17] showed that intervention studies in very frail and multimorbid populations cannot support the beneficial effect of exercises on functional performance and hence suggest that the degree of frailty might be critical, when reviewing the effectiveness of exercising [17]. Confirming these findings, a study with a moderate intensity group-exercise program positively influenced the reduction of falls and improved physical performance in pre-frail, but not in frail elderly nursing home residents [18]. Contrary to the findings in community-dwelling older individuals [18–20], exercise interventions have not been able to reduce falls in nursing homes [21]. Nevertheless, a few studies showed a positive impact of exercise on ADL [1, 16] and functional capacity [12, 16, 22–24] for people living in nursing homes. A systematic review investigating frail older people in nursing homes, residential care, and in the community [25] demonstrated that most studies provide evidence that exercise interventions have a positive impact on frailty. However, the definition of the term ‘frailty’ was different and unclear among most studies. Moreover, in the majority of studies, effect sizes were small [1] and a clear recommendation for an appropriate intervention was not given.

For cognitive outcomes and dementia, several studies with nursing home residents indicated no differences between exercise and cognitive intervention groups compared to the control group [26–31]. However, the findings also demonstrate a prominent heterogeneity regarding type, duration and frequency of exercise and severity of participants’ dementia. On the other hand, some studies addressing physical training and exercises reported positive effects on cognitive performance (short-term memory recall, visuospatial abilities, multiple aspects of executive functions) in the setting of nursing homes [1, 22, 23, 32–34]. The analysis of previous studies [1, 22, 23, 26–34] indicates that programs using higher intensities (e.g., walking exercises with additional weights) and longer training periods (> 3 months; at least twice a week [35]) tend to have a greater impact on cognitive performance. Moreover, most benefits on motor and cognitive performance seem to be reached by dual-task training interventions [35].

For quality of life, exercise interventions have shown to improve older adults’ well-being [23, 36], particularly depressive symptoms were reduced in people with dementia [37]. However, a large RCT, aimed at reducing depressive symptoms to increase well-being among nursing home residents, conducted a moderately intense exercise program twice a week for 12 months and found no effect [38]. A high-intensity functional exercise program aiming to reduce depressive symptoms and improve psychological well-being showed no effect among older people living in residential care facilities, but positive effects among people with dementia [36]. Nevertheless, there is neither consistent evidence, nor evidence-based physical activities, nor exercise guidelines to promote health-related outcomes (like physical and cognitive functioning and quality of life) for very old, multimorbid, and institutionalized people [39–41]. Despite the insufficient evidence, a recent report from the International Association of Gerontology and Geriatrics - Global Aging Research Network (IAGG-GARN) and the IAGG European Region Clinical Section provides first recommendations for physical activity in older persons, who are in need of care [41]. To lower the risk of developing a number of disabling medical conditions and various chronic diseases, they propose a multicomponent program administered in small groups, including training of strength, endurance, mobility, and balance, in combination with dual-task exercises in moderate intensities twice a week for 35–45 min each. The report also emphasizes continuously adapted training intensities in relation to the residents’ abilities. Also, progressive enhancement, inclusion of stimulating materials and music, as well as training for movements that are often associated with falls (e.g., walking forward with changes of direction) is advised. In addition, the preferences and needs of the individuals should be discussed in advance, in order to define feasible goals and to take the residents’ self-efficacy into account [42].

Overall, the effectiveness of preventive interventions in nursing homes which address these recommendations and cognitive-motor exercises is assumed, but not yet examined. Thus, more high-quality studies are needed to examine and to structure results of preventive interventions, so they can be implemented into the health care system [42].

### Aims and research questions for the study

Based on the existing research and the physical activity recommendations mentioned above, a multicenter intervention study will be conducted, aiming to determine the feasibility and efficacy of a multicomponent exercise intervention program for residents of nursing homes. Moreover, we assume that these effects will improve the residents’ quality of life.

## Methods/design

The SPIRIT statement [43] was used as a guideline for this protocol paper.

### Trial design

This study is a two-arm single-blinded randomized controlled trial of an individually tailored multicomponent intervention (see Table 1) for older men and women living in nursing homes. The study will be aptly named PROCARE – Prevention and occupational health in long-term care, as part of the PROCARE project. A stratified randomization is performed after the baseline assessment. The assessment of primary and secondary outcomes takes place in all subjects upon entry to the study (T1) by a blinded assessor and is repeated at 16 weeks (T2), and at 32 weeks (T3, retention test, intervention group only) after randomization (see Table 2). *The trial is registered at DRKS.de with registration number* DRKS00014957.

**Table 1 Tab1:** Description of the intervention

Program	Week 1–4	Week 5–8	Week 9–12	Week 13–16
Mobilisation and warm-up	e.g., range of motion exercises for the wrists, hip, shoulders, knees, and ankles	Cf. week 1–4	Cf. week 1–4	Cf. week 1–4
Coordination, balance, and cognitive exercises	e.g., standing balance, bodyweight shifting, motivational cognitive-motor games with group interaction including balls and scarfs	e.g., standing balance, bodyweight shifting, motivational cognitive-motor games with group interaction including balls and scarfs	e.g., standing balance with feet together, side-by-side, bodyweight shifting, motivational cognitive-motor games with group interaction including balls and scarfs	e.g., standing balance with feet together, side-by-side, semi-tandem, tandem, standing on one leg, bodyweight shifting, motivational cognitive-motor games with group interaction including balls and scarfs
Dual-task walking exercises (endurance)	150-180 m e.g., brisk walking, starting, stopping, avoiding obstacles, turns	180-240 m e.g., brisk walking, starting, stopping, avoiding obstacles, turns	240-300 m e.g., brisk walking, starting, stopping, avoiding obstacles, turns, dual-task conditions e.g., carrying a cup, repeating rows of numbers, paying attention to signs	300-330 m e.g., brisk walking, starting, stopping, avoiding obstacles, turns, dual-task conditions e.g., carrying a cup, repeating rows of numbers, paying attention to signs
Calm down	e.g., stretching and relaxing exercises	Cf. week 1–4	Cf. week 1–4	Cf. week 1–4

**Table 2 Tab2:**
[figure not shown]
Schedule of enrolment, interventions, and assessments

### Participants, interventions, and outcomes

#### Ethics approval

The trial is conducted in agreement with the principles of the Declaration of Helsinki and the guidelines of Good Clinical Practice (GCP). All participants or their legal guardians give written informed consent prior to the study enrollment. The ethics committee of the Hamburg Chamber of Physicians, Germany, has approved the study protocol *(PV5762).*

#### Recruitment of nursing homes

Eight cities and their surroundings throughout various regions in Germany (Bremen, Chemnitz, Frankfurt, Hamburg, Karlsruhe, Nuremberg, Paderborn and Stuttgart) will recruit 48 nursing homes in total (six per site). The institutions involved are deliberately selected based on their basic structural figures (number of nursing places, number of employees, urban or rural district, social-economic status), in order to analyze the applicability of the program under a wide range of conditions. Therefore, a list of all nursing homes will be created. It will then be stratified by their structural characteristics and afterwards the nursing homes will be randomly selected. Participation is voluntary and will not be remunerated. In case a requested nursing home declines to participate, another facility with similar characteristics will be requested instead.

#### Recruitment of participants

Assessment of eligibility and recruitment of participants with respect to inclusion and exclusion criteria will be primarily based on nursing documentation and staff consultation. Care management and lead investigators will meet to discuss and create a list with suitable nursing home residents, prior to the study enrollment. It will be made clear that the intervention is targeting everyone who meets the inclusion criteria and not only those who are very open to physical activities and therefore might be more likely to show a positive response to the intervention. Even the very institutionalized, frail residents will be encouraged to participate. Nevertheless, it is a voluntary intervention and there is still room for bias because the individual reasons for participation will remain unclear. After the selection process, nursing staff will inform all suitable residents or their legal guardians about the study goals and ask for voluntary participation. All verbally consented participants or their legal guardians will give written informed consent prior to the study enrollment.

#### Eligibility criteria

Inclusion criteria are *i)* willingness to participate, *ii)* ability to participate in group activities, *iii)* ability to sit unassisted on a chair or in a wheelchair, and *iv)* the ability to understand and execute simple instructions. No other inclusion or exclusion criteria will be applied.

#### Assignment of interventions

Assessment and data collection will be done by blinded assessors in a strictly pseudonymized form to guarantee a blinded data analysis.

To avoid performance bias, the measurements and the intervention follow a standardized protocol. All participant information and data will be stored securely and identified by a coded ID number only to maintain the participants’ confidentiality.

To avoid selection bias, a stratified randomization will be conducted to divide the participants into either an intervention group or a waiting time control group. The random allocation will be stratified and executed by lot by the director of the study who will receive the pseudonymized codes of the participants and their baseline characteristics and will not be involved in neither the assessment nor the intervention procedures. Stratification will be based on comparable sex, age, and cognitive performance (according to the Montreal Cognitive Assessment MoCA-Score [44]) to avoid differences in the baseline characteristics of the groups. After assigning the participants to either the intervention or waiting time control group, the pseudonymized participant codes will be sent to the study investigators who are responsible for the data management. The exercise scientist or physiotherapist, who will conduct the intervention, will receive only names of the participants in the intervention group and after 16 weeks names of the waiting time control group without being aware of the control group design.

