#### Secondary outcomes

The following secondary outcomes will be measured to evaluate the efficacy of the intervention program:

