##### Physical functioning

The *Barthel Index* [50] is used to systematically record the independence of participants when performing basic ADL via ten items. Feeding, personal toileting, bathing, dressing and undressing, getting on and off a toilet, controlling bladder, controlling bowel, moving from wheelchair to bed and returning, walking on level surface (or propelling a wheelchair if unable to walk) and ascending and descending stairs are rated on a scale from 0 to 15 points depending on the item. Total possible scores range from 0 (totally dependent) to 100 (fully independent) [50].

*Hand Grip Strength* is measured with a hydraulic hand dynamometer (JAMAR, hydraulic hand dynamometer). Three trials with each hand will be executed. Results will also be used to assess the frailty index item weakness.

The *Functional reach* [51] is a clinical measure of balance. It assesses the difference between the arm’s length and maximal forward reach in cm, using a fixed base of support. The test will be executed in a sitting position. The participant sits against the back of a chair next to a wall reaching forward as far as possible without losing balance. Reach distance will be measured with a scale attached to the wall.

For the measurement of *Frailty* this study will apply the original operationalization of the Frailty Phenotype from the Cardiovascular Health Study [52] to enable comparability. A frailty index will be formed out of five measured factors, including an unintentional weight loss of more than 4.5 kg in the past 12 months (shrinking), BMI- and sex-adjusted hand grip strength (weakness), frequency of fatigue in the last week by using two items of the Center of Epidemiological Studies-Depression Scale (CES-D, exhaustion), height- and sex-adjusted gait speed (slowness) and sex-adjusted energy expenditure by physical activity (modified Minnesota Leisure Time Physical Activity Questionnaire).

The short form of the *Falls Efficacy Scale-International* (Short-FES-I) [53] is a seven-item questionnaire with a scoring range between one and four, which provides information on the level of concern about falls for a range of activities of daily living. The number of falls, fall-related injuries and deaths occurring during the 32-week period will be documented by nursing staff.

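### Data collection is described as blinded without exception, but falls, fall-related injuries and deaths are recorded by nursing staff who are unlikely to be blind to allocation

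*Protocol article*

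**What the plan says.** Under Assignment of interventions the protocol article says: "Assessment and data collection will be done by blinded assessors in a strictly pseudonymized form to guarantee a blinded data analysis". No outcome is excepted. The Trial design section calls the trial single-blinded and has the primary and secondary outcomes assessed "upon entry to the study (T1) by a blinded assessor and is repeated at 16 weeks (T2"), with a further test at 32 weeks in the intervention group only.

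Under Secondary outcomes, Physical functioning, the last sentence of the paragraph on the short Falls Efficacy Scale names a different recorder: "The number of falls, fall-related injuries and deaths occurring during the 32-week period will be documented by nursing staff". That section opens with: "The following secondary outcomes will be measured to evaluate the efficacy of the intervention program".

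Three other statements bear on what nursing staff know:

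- Recruitment of participants: "nursing staff will inform all suitable residents or their legal guardians about the study goals and ask for voluntary participation".
- Assignment of interventions: "a stratified randomization will be conducted to divide the participants into either an intervention group or a waiting time control group", so the unit of randomisation is the resident and not the home.
- Abstract, Methods: "For a period of 16 weeks the training group will meet twice a week for group-based sessions".

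The article does not say that nursing staff are kept unaware of allocation, or that a blinded person checks or classifies their fall records.

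**The concern.** Taken as written, the two statements about who collects data cannot both be true. The conflict matters because a count of falls depends on its recorder. Whether a slide to the floor or an unwitnessed event is noticed and written down, and whether a bruise is put down to a fall, involves judgement. A recorder who knows the aims of the study and who trains may record differently in the two arms. Belief that training prevents falls could lower the count among exercisers, while closer attention to exercisers could raise it. The data themselves would not show which had happened.

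Falls are a secondary outcome, but they carry some weight. The Intervention section says training concentrates on everyday situations linked to fall risk. The Monitoring section expects no adverse events and sets up no monitoring committee. Falls, fall-related injuries and deaths are thus the only harm-type events that the article names for recording.

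**Working it through.** The article gives no fall rate and no figure for completeness of recording, so there is nothing of the plan's to reproduce. The check is a comparison of text, followed by an illustration on assumed values.

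**1. Who records.** The blinding sentence covers assessment and data collection, by blinded assessors. The falls sentence assigns documentation to nursing staff. Nothing elsewhere makes the staff blinded assessors or puts a blinded step between their record and the analysis.

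**2. What the recorders know.**
- Study goals: stated, since nursing staff explain them when inviting residents.
- Allocation: not stated, but a strong inference. Individuals are randomised and one arm attends group sessions twice a week for 16 weeks.
- Both arms in the same home: also inferred. Stratification is by sex, age and cognitive score, and the home is not mentioned. The figures fit, however: 1120 / 48 = 23.3 residents per home, and 23.3 / 2 = 11.7 per arm, which lies within the stated training group size of 4 to 15.

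**3. Which period.** Falls are counted over 32 weeks. The instructor receives "after 16 weeks names of the waiting time control group without being aware of the control group design". Of the 32 weeks, 32 − 16 = 16 fall after that handover, when the control arm may itself be in training. Only weeks 0–16 compare trained with untrained residents.

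**4. How unequal recording acts.** Let r be the share of falls that are written down and c the share of those that are then classified as falls, in the intervention (I) and control (C) arms:

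recorded ratio = true ratio × (r_I / r_C) × (c_I / c_C)

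With a true ratio of 1.0, equal classification (c_I = c_C) and **assumed** recording shares:

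| r_I | r_C | Recorded ratio |
|---|---|---|
| 80% | 100% | 0.80 |
| 80% | 90% | 0.80 / 0.90 = 0.89 |
| 90% | 100% | 0.90 |
| equal | equal | 1.00 |
| 100% | 90% | 1.00 / 0.90 = 1.11 |
| 90% | 80% | 0.90 / 0.80 = 1.13 |
| 100% | 80% | 1.00 / 0.80 = 1.25 |

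The table shows how sensitive the ratio is. It does not estimate the bias in this trial. For deaths, both shares should be close to 100% in each arm and the ratio is hardly disturbed. The same holds, to a lesser degree, for falls that lead to medical treatment or hospital transfer.

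**5. What blinded classification can do.** It brings c_I / c_C towards 1. It leaves r_I / r_C as it was, because a fall that was never written down never reaches the assessor.

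**The case against.** The best defence is that the blinding sentence was meant only for the scheduled tests. The Trial design section ties the blinded assessor to the T1 assessment and its repeats, and the paragraph after the blinding sentence speaks of standardised measurements. The article also names nursing staff openly as recorders, so nothing is concealed. This reading is plausible and may well be the intent. But the sentence says data collection without limit, and it is the sentence a reader would cite for the trial's blinding. If the narrower scope was intended, the repair is short.

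It is also fair to say that nursing staff are the practical people to record falls and that a fall definition and event form may sit in the full protocol, which is not shown. Both points stand. No fault is found here with the choice of recorder or with the absence of a form from the article.

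A reader might infer more than the text supports:

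- That falls are the main harm outcome. The article lists them among secondary outcomes measured for efficacy and gives them no such label.
- That nursing staff cannot be blind. Their knowledge of the goals is stated, but their knowledge of allocation is inferred. Unlikely to be blind is as far as the text goes.
- That fall results would be published as blinded. The article does not say so.

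**Conclusion.** The concern holds in a limited form. The blinding statement is wider than the procedures described, and falls, fall-related injuries and deaths do not have the protection it claims. For deaths the practical consequence is close to nil. For minor or unwitnessed falls, differential recording is possible, in an unknown direction and of unknown size. The ratios of 0.80 to 1.25 shown above rest wholly on assumed recording shares of 80% to 100%.

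The conclusion rests on two inferences: that both arms live in the same homes, and that staff can see who attends. Both are likely, given individual randomisation and regular group sessions, but neither is stated. The primary analysis (SPPB, gait variables, Serial Sevens and Verbal Fluency) does not use these records and is unaffected.

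**What to change.** 1. In Assignment of interventions, limit the blinding claim to the scheduled tests that are compared between arms, T1 and T2. T3 covers the intervention group only, so it has no between-arm comparison to protect. State that falls, fall-related injuries and deaths are recorded by nursing staff who are not blinded to allocation.
2. Keep nursing staff as recorders, but have the existing blinded assessors classify fall and injury from pseudonymised event records that do not mention training.
3. Limit the between-arm fall comparison to weeks 0–16, before the waiting-list names go to the instructor. Later falls can be described within each arm.
4. Report falls needing medical treatment or hospital transfer alongside all recorded falls, as a check less open to recording bias.

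The first change costs a few sentences. The second costs some coding time from assessors already in the trial, and it reduces classification bias only: falls that were never recorded stay missing. The third gives up half the counting period for the comparison. The fourth rests on fewer events, so its interval will be wider. It is therefore best used as a check beside the full count and not in its place.

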Discontinuation of the intervention may occur in case of health decline or if a participant wishes to stop taking part in the group intervention. To improve adherence and to promote retention, the therapists will give explanations about the purpose of the intervention and the possible benefits of the exercises. Attendance of each participant will be recorded and reasons for drop outs will be documented. No other concomitant group exercise interventions are permitted besides usual care and physiotherapy. Control group participants will be asked to continue their regular everyday activities.

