### Data collection, management, and analysis

#### Statistical analysis

We will evaluate the effects of the intervention on every quantitative, qualitative, and ordinal outcome, using repeated measures or mixed models, “t” tests, Kruskall-Wallis Mann-Witney tests or the Chi-square tests, depending on the type of outcome and their normal or non-normal distribution. The primary analysis will be a mixed model between-group comparison of the SPPB, gait variables, Serial Sevens, and Verbal Fluency Test, utilising all available data points during follow-up. We will use the Bonferroni correction to appropriately adjust the overall level of significance for multiple comparisons. Between-group differences for all primary and secondary outcomes will be adjusted for baseline values, age, sex, and education. Secondary outcomes will be analysed with similar methodology, using repeated measures mixed model between-group comparisons. All statistical analyses will be performed using SPSS Statistics for Windows (version 25.0, IBM). Statistical significance level is set at *p* < 0.05.

Intention-to-treat analysis will be performed (participants who are randomized into groups after the collection of baseline data). For the intention-to-treat analysis, data of all trial patients in the groups to which they were randomized will be processed, regardless of whether they received or adhered to the allocated intervention. It is assumed that the majority of participants in the two arms will receive the appropriate number of intervention sessions. In addition, a per-protocol analysis of the participants who completed the study without major protocol violation (e.g., who attended more than 80% of the training sessions), will be performed. The per-protocol analysis will be performed as a secondary analysis, if there is a sufficient number of participants in the two arms, who do not receive the intervention protocol or are lost to outcome assessment. Data from those participants, who do not violate the treatment protocols, will be included in the per-protocol analysis. The multiple imputation (MI) technique will be used for dealing with missing data under the assumption that data are missing at random.

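### Pseudonymised data cannot guarantee a blinded analysis of any file that holds the intervention-only T3 visit, and the primary model appears to include it

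*Protocol article*

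**What the plan says.** Assignment of interventions makes the claim: "Assessment and data collection will be done by blinded assessors in a strictly pseudonymized form to guarantee a blinded data analysis". The same section says that, once residents have been allocated, "the pseudonymized participant codes will be sent to the study investigators who are responsible for the data management". It adds that the trainer receives the intervention names at the start and "after 16 weeks names of the waiting time control group without being aware of the control group design".

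Trial design places the last visit "and at 32 weeks (T3, retention test, intervention group only) after randomization". The abstract agrees: outcomes "will be assessed in both study groups at baseline (pre-test), after 16-weeks (post-treatment), and after 32-weeks (retention test, intervention group only". T1 and T2 therefore exist in both arms, and T3 in one.

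Statistical analysis describes the primary between-group mixed model as "utilising all available data points during follow-up". Sample size estimate / power calculations is built on two groups and three measurements. It gives 1120 residents, 70 per group in each of eight centres, with a 30% allowance for loss.

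On attendance, the Intervention section says: "Attendance of each participant will be recorded and reasons for drop outs will be documented". Statistical analysis uses attendance above 80% of sessions as its example of having no major protocol violation.

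**The concern.** A pseudonym replaces a name. It does nothing to conceal allocation if the record itself shows which arm it belongs to. A visit held in one arm only does exactly that, and the article's wording appears to bring that visit into the primary model.

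What is at stake is the protection of choices made after data are seen. Statistical analysis leaves several of these open. The test depends on the observed distribution, a major protocol violation is defined only by example, and the per-protocol analysis depends on whether enough residents deviate. The article does not say that the blind exists to protect these choices. Still, this is what an analysis blind is normally for, and a trial report that repeated the guarantee would claim a safeguard that the described mechanism does not provide.

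**Working it through.** The plan gives no figure for the strength of the blind, so there is none to reproduce. The check is one of record structure: which data are present in one arm only, and how much they reveal.

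**Inputs**
- Residents per arm: 70 × 8 = 560, and 2 × 560 = 1120 (Sample size estimate / power calculations).
- T3: intervention arm only (Trial design; abstract).
- Loss *d* in the intervention arm by T3: 30%, the plan's 20% + 10%. Applying it to that arm by T3 is an assumption, so *d* is varied from 10% to 40%.

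**Case 1: the file includes T3 and masked A/B labels.** One label has T3 records and the other has none. The label without them is the control arm. Both labels are identified for all 1120 residents at any loss below 100%.

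**Case 2: the file includes T3 but no arm column.** Guess intervention if a T3 record is present, control otherwise.
- P(intervention | T3 present) = 1.
- P(control | no T3) = 560 / (560 + 560*d*).
- Share classified correctly = (560(1 − *d*) + 560) / 1120.

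At *d* = 30%, intervention residents with T3 number 560 × 0.70 = 392, and those without number 168. Then P(control | no T3) = 560/728 = 0.77, and the share correct is (392 + 560)/1120 = 952/1120 = 85%.

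| Loss *d* | Intervention residents with T3 | P(control given no T3) | Classified correctly |
|---|---|---|---|
| 10% | 504 | 0.91 | 95% |
| 20% | 448 | 0.83 | 90% |
| 30% | 392 | 0.77 | 85% |
| 40% | 336 | 0.71 | 80% |

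**Case 3: the file holds T1 and T2 only, with masked labels and no attendance.** Both visits are scheduled in both arms. Visit structure carries no information on arm, and guessing from it is right 50% of the time at 1:1 allocation. This file can be blinded.

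**Attendance.** In weeks 1 to 16 the trainer holds only intervention names, and control residents are asked to carry on as usual. Control names follow after week 16. Session records dated to weeks 1 to 16 are therefore one-sided, by inference from these passages. An undated attendance total need not be.

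**The case against.** The strongest reply is that T2 is the only follow-up visit at which the arms can be compared. A sensible analyst would make that comparison on T1 and T2 with masked labels, and the blind would hold. How labels are masked and released is detail that an article commonly leaves to the full protocol or analysis plan. Both arguments have force, and the absence of an unblinding procedure is not the point here. What remains is that the article names pseudonymised collection by blinded assessors as the means that guarantees the blind, and describes a primary model whose wording takes in T3. Those means cannot deliver that property for that file.

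Some stronger inferences are tempting but are not supported:
- *Attendance exists for the intervention arm only.* The article records it for each participant, has the waiting group's names passed to the trainer later, and expects sessions in both arms. Only dated or week 1 to 16 attendance is one-sided, and no passage says that it enters the analysis file.
- *Every analysis file reveals allocation.* Case 3 is a counterexample.
- *There is no blind at all.* Nothing cited undermines assessor blinding at T1, which precedes randomisation, or at T2.
- *T3 exposes practically everyone even without labels.* At 30% loss, 168 intervention residents lack T3 and look like controls.
- *Data managers are told the arm.* The codes are sent to them, but the article does not say that the codes carry the allocation, or that data managers are the analysts.

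It is also fair to say that no estimate, error rate or sample size is shown to change, and that loose analysis choices are a matter of pre-specification that a blind would not cure by itself.

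**Conclusion.** The point holds in a limited form. The guaranteed blind cannot hold for a data set that includes T3 or dated week 1 to 16 attendance. The wording on follow-up data, with the three assumed measurements, appears to put T3 in the primary file. If it does, masked labels are revealed completely. Without labels, about 85% of residents are classifiable at 30% loss (80% to 95% for losses of 40% down to 10%).

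This rests on two assumptions: that all available follow-up data means what it says and so includes T3, and that the planned loss applies to the intervention arm by T3. The first decides whether the primary analysis is affected. The second changes only the percentage.

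T3 assessment is in a similar position. Everyone measured there has been allocated to training, so an assessor who knows the design is not blind at that visit.

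Severity is minor. The claim needs correcting, and the analysis can be arranged so that a narrower claim is true.

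**What to change.** 1. Run the primary between-group analysis on a file holding T1 and T2 only, with random A/B labels and without T3, attendance or events from weeks 17 to 32.
2. Fix outcome handling, model choice and imputation on that file. Write the per-protocol rule down before unblinding.
3. Lock the T2 intention-to-treat analysis.
4. Then release the arm key, T3 and attendance, and apply the per-protocol rule only at that stage. Attendance-based flags must not reach the blinded analyst, because before T2 only the intervention arm has sessions to miss and the flags would themselves show the arm.
5. In Assignment of interventions, limit the blinded-analysis claim to this T1/T2 analysis and replace the word guarantee with the procedure. State whether the codes sent to data management carry the allocation. Describe T3 assessment and analysis as open.

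The cost is a change of protocol wording and one extra data export. The T3 and per-protocol analyses have to follow the T2 lock.
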